#### Independent variables

*Socio-demographic and clinical profile:* age; gender; relationship status; country of birth; religion; paid work; TPAL; baby’s birth weight; weeks of gestation at birth; maternity leave; partner leave to care for the baby; maternal pathology and neonatal pathology.*Newborn variables:* type of feeding in hospital and at 1 month of the child’s life; in the case of MF or FF, indicate how much infant formula you feed your baby daily, in ml; number of bottles or syringes of infant formula you give your baby daily; how many ml does each bottle or syringe have.*Breastfeeding accessories:* use (and quantity in case of several) of a breast pump; milk storage containers; bags to store milk; nipple shields; a nursing supplementer; cans of infant formula; bottles; brushes to clean the bottles; a bottle warmer; a bottle sterilizer; paediatric nasogastric tubes; reusable nursing pads and disposable nursing pads.*Mother's nutrition variables**: **a) Eating habits:* type of diet; taking any vitamin supplements; usual place to purchase food, transport of food and distance from home; type of energy used for cooking; members of the family who usually cook and how much of the food is thrown away? *b) Recording of the mother's daily diet (recall 24 h)* [33, 34] (validated in other studies [35, 36]), *and food consumption habits:* type of food: portions, packaging, type of cooking, characteristics of the product (fresh, frozen), origin of the product, condiments and beverages.

The maternal diet will be measured in terms of macronutrients (carbohydrates, proteins and fatty acids in grams), micronutrients (calcium, magnesium and in milligrams, vitamin D in micrograms) and energy consumed in kcal).

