Globally, water scarcity presents a significant challenge in fulfilling the need for freshwater for drinking and agricultural purposes [16]. In Spain, food consumption is associated with a water wastage of 3,302 L per person per day. The most substantial environmental impact from water use is attributed to the production of meat, fish, and animal fats (26%), as well as dairy products (21%) [17]. The water footprint of food waste was estimated to be 2,095 hm^3^, equivalent to 131 L per person per day [17]. Given the heightened water stress, this study also assesses the water stress implications of the life cycle of formula production, infant feeding accessories, and maternal dietary practices. There is currently no rigorous data on the GHG savings that Europe could achieve by taking into account the dietary habits of postpartum mothers if BF was their top choice rather than FF. To meticulously compare the contribution of EBF and FF to global warming in terms of their carbon footprint, the various dietary patterns of postpartum women and the accessories required for breastfeeding must be considered. Although there is no consensus on the need to supplement the diet of lactating mothers, it is recommended that they increase their daily calorie intake by 500 kcal to cover the nutritional and energy requirements of feeding their baby [18, 19]. Additionally, to promote public health, the Catalan government issued specific nutritional guidelines for pregnant women [20].

Currently, 92% of mothers want to breastfeed their babies but only 17% do EBF for six months [21]. Stopping BF is most often not the mother’s wish and happens earlier than desired. The most frequent causes of stopping breastfeeding are social barriers [22]. Mothers and families need support to ensure that their children receive optimal BF during the first six months of life, as well as the progressive and appropriate introduction of complementary feeding. Healthcare professionals play an essential role in providing this support [23].

The WHO recommends the support of health services in providing advice on infant and child nutrition. It is committed to supporting countries in accordance with the Global Nutrition Targets approved by Member States [24]. One of these targets is to increase the rate of EBF during the first six months of life to at least 50% [24].

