In the 2019 document *Green Feeding Europe*, the Council of the European Union makes a collaborative effort with institutions to inform and involve the Green Parties of Europe, so they include the nutrition of infants and young children in their environmental programmes [12].

In the face of the climate emergency, it is crucial to understand the impact of maternal diet on health and the environment. A change towards a healthier and more environmentally friendly diet should be promoted, while increasing the rates of exclusive breastfeeding can be considered an issue related to public health, social rights, and inequality. Government investment and changes in these areas must be achieved, including longer maternity leave, spaces where women can breastfeed freely and comfortably, the monitoring of surrogate advertising, more promotion of breastfeeding and access to professionals.

To our knowledge, there are no studies on the environmental benefits of breastfeeding, or the quality and type of diet followed by postpartum women in Catalonia, Spain. Therefore, measuring the environmental benefit of breastfeeding may help protect the environment and consequently the health of the population and the planet [25, 26].

This project is split into two independent sequential projects. The results from Phase I will bolster the development of educational materials to be used in Phase II (educational intervention to improve prevalence of breastfeeding and a sustainable diet).

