#### Objectives of the study

Primary objective

Determine the environmental impacts (climate change, water consumption and water scarcity) of EBF, MF and FF of postpartum mothers in their baby’s first month of life, taking into account the accessories used for infant feeding and mother´s diet and food consumption habits.

Secondary objectives:

To calculate the prevalence of EBF, FF and MF after birth, and at 4–6 weeks postpartum.To describe the maternal diet in terms of macro, micronutrients and energy consumed.To compare the calories consumed by according to the type of breastfeeding, lactating mothers (EBF and MF) and non-lactating mothers (FF).To compare feeding types with socio-demographic and clinical data.To compare maternal diet and food consumption habits with feeding type and socio-demographic data.

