**Fig. 1 Fig1:**
[figure not shown]
Environmental impact factors considered in the GREEN MOTHER I project. Legend: EBF – exclusive breastfeeding; MF – mixed feeding; FF – formula feeding

For the descriptive statistics, the qualitative variables will be described with their absolute and relative frequencies and quantitative variables with their mean and standard deviation or with their median and quartiles. In the comparison of proportions, we will use the Pearson Chi Square test and in the comparisons in quantitative variables the analysis of variance or the Kruscal-Wallis test (with post-hoc analyses), depending on the conditions of application. The level of significance will be 5% and the analyses will be performed with the statistical package STATA v.18.

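### Maternal diet is compared across feeding types in absolute amounts with no energy term, so the nutrient comparisons cannot tell eating more from eating differently

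*Protocol article*

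**What the plan says.** Three parts of the protocol article bear on this.

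- **Independent variables** sets the units: "The maternal diet will be measured in terms of macronutrients (carbohydrates, proteins and fatty acids in grams), micronutrients" in milligrams or micrograms, ending with "vitamin D in micrograms) and energy consumed in kcal". Neither percent of energy nor any nutrient density is mentioned.
- **Objectives of the study** has three relevant secondary objectives. One is descriptive: "To describe the maternal diet in terms of macro, micronutrients and energy consumed". One compares calories between "lactating mothers (EBF and MF) and non-lactating mothers (FF"). One is a wider comparison: "To compare maternal diet and food consumption habits with feeding type and socio-demographic data". The last does not state a scale.
- **Data analysis plan** (text after Fig. 1) names "in the comparisons in quantitative variables the analysis of variance or the Kruscal-Wallis test", with post-hoc analyses, at the 5% level. It names no covariate.

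The **Background** anticipates a difference in energy. It says a theoretical 500 kcal increase in the mother's diet has to be counted and, after noting that there is no consensus on supplementing lactating mothers, that "it is recommended that they increase their daily calorie intake by 500 kcal". **Expected outcomes** also refers to an increase in maternal diet that compensates for breastfeeding. The gap in knowledge that the Background names includes "or the quality and type of diet followed by postpartum women in Catalonia, Spain".

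**The concern.** The absolute intake of a nutrient is energy intake multiplied by the amount of that nutrient per kcal. If one group eats more of the same diet, all its nutrient means go up by the same factor. A series of tests on grams, milligrams and micrograms across EBF, MF and FF would then largely show one fact, the difference in energy, which has its own secondary objective. Those tests could not show whether the diets differ in composition, which is part of what a question about quality and type of diet asks.

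This follows from the scale of the variable. It is not confounding by the kind of woman who chooses each feeding type, and it would remain with perfectly comparable groups.

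What is at stake is interpretation. Phase II educational materials on nutrition are to be based on Phase I results. A list of nutrients that differ by feeding type could be taken as evidence that the diets differ in kind, when the groups may differ only in how much they eat.

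**Working it through.** **The plan's own figures.** The protocol gives no figure for the nutrient comparisons, only for the carbon footprint. That one reproduces: a three-group ANOVA with n = 60/60/30, SD 1, a largest difference of 0.7 and equally spaced means has 81.9% power, against the stated 80%. The expected counts also reproduce: 400 × 0.64 = 256, 400 × 0.23 = 92 and 400 × 0.13 = 52. After the tolerated 35% loss they are about 166/60/34.

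**Proportional shift.** At equal composition, the ratio of absolute nutrient means equals the ratio of mean energies, (E + Δ)/E. The 500 kcal is from the Background. The non-lactating intake E is an assumption, as the document gives none.

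- E = 1,800: 500/1,800 = 27.8%
- E = 2,000: 500/2,000 = 25.0%
- E = 2,200: 500/2,200 = 22.7%

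**How often the tests would be significant.** This needs further assumptions, none of them in the document: mean FF energy 2,000 kcal, one-day energy SD 600 kcal, lognormal energy, and an independent lognormal nutrient density with the same mean in all three groups. EBF mothers eat Δ kcal more, and MF mothers eat half of Δ or all of it. Absolute intake is energy × density. The table shows the percentage of one-way ANOVAs with p < 0.05 (4,000 runs per setting; ranges cover the two MF patterns).

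| Group sizes | Δ (kcal) | density CV 0.25 | CV 0.4 | CV 0.8 |
|---|---|---|---|---|
| 256/92/52 | 500 | 95–97 | 75–81 | 27–30 |
| 256/92/52 | 250 | 41–48 | 25–27 | 9–10 |
| 256/92/52 | 100 | 10–11 | 7–8 | 5 |
| 256/92/52 | 0 | 5 | 4 | 4–5 |
| 166/60/34 | 500 | 82–87 | 57–61 | 16–19 |
| 60/60/30 | 500 | 67–74 | 43–46 | 15–16 |

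Repeat runs of the 500 kcal, CV 0.8 setting at 256/92/52 spread over about 26–32%. With an energy SD of 500 instead of 600, the first row becomes 98–99, 81–86 and 27–31.

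Tested per kcal, the same simulated data give 4–6% in every setting, as they should when composition is equal.

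**Reading the two percentages.** The high figures are power to detect a true difference in amount. The 4–6% is the error rate for a different question, whether composition differs. Set side by side, they show that the two scales answer different questions. They do not show that the absolute test is invalid.

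**The case against.** The case against has several parts, and much of it stands.

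- **The quoted sentence gives measurement units, not an analysis scale.** The nutrient objective is descriptive, the comparison objective names no scale, and no part of the article rules out energy adjustment. Energy is recorded, so adjusted values can be derived, and Annex II or an analysis plan may provide for them. A reader might infer that the plan commits to testing each nutrient in grams or milligrams and nothing else. The document does not say so. What remains is that the text offers only absolute units and only tests without an energy term, for a comparison where energy is anticipated to differ.
- **The 500 kcal is not an expected observed difference.** The Background calls it theoretical and recommended, and notes the lack of consensus. A reader might infer that EBF mothers will in fact eat 500 kcal more. That is unknown, which is why calories have their own objective.
- **A higher absolute intake is real.** A reader might call the resulting significant tests false positives. They are not: a mother who eats 25% more of the same diet does take in 25% more protein and calcium. Absolute amount is a sound scale for intake and adequacy, and quantity eaten feeds the environmental outcome. Only reading it as composition would be wrong, and the authors do not say they will.
- **Not nearly every nutrient would be affected.** That stronger reading needs the full 500 kcal and modest between-woman variation. It fails for highly variable nutrients or a smaller excess, and weakens at the minimum group sizes.
- **Diet type is also recorded in other ways**, such as type of food, cooking and origin, so nutrient amounts are not the only evidence on quality.

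None of this removes the central point: as written, the nutrient comparison cannot separate quantity from composition.

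**Conclusion.** The point holds as a cheap improvement to one secondary objective. The protocol article pairs absolute units and tests without an energy term with a comparison in which it anticipates different energy intakes. At identical composition, a full 500 kcal excess raises every absolute nutrient mean by 23–28%, on an assumed non-lactating intake of 1,800–2,200 kcal.

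At 256/92/52 with an energy SD of 600 kcal, the share of nutrient tests reaching 5% runs from about 75–97% (+500 kcal, density CV 0.25–0.4), through about 26–32% (+500 kcal, CV 0.8), to about 9–48% (+250 kcal, CV 0.25–0.8). It is near 5% when there is no excess. Baseline energy, SD, CVs, the excess actually eaten and the MF pattern are all assumptions, so these figures show a range of possibilities and are not a forecast.

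The primary environmental outcome and the sample size are not touched.

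**What to change.** Keep absolute intakes for the descriptive objective and for comparing intake. For the comparison of maternal diet with feeding type, add macronutrients as percent of energy and micronutrients per 1,000 kcal, or include energy as a covariate. State that conclusions on composition will rest only on the energy-adjusted results, and leave the question of quantity to the kcal comparison and the absolute amounts. Write this down before the analysis, so that the scale is not chosen after seeing which one is significant.

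The cost is a sentence or two and a few more secondary comparisons to report. Energy and nutrients both come from the 24-hour recall already planned, so no new data are needed. Replacing the absolute comparison altogether is not recommended, because it answers a legitimate question of its own.

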## Data analysis plan and expected outcomes

### Data analysis plan

The environmental impacts of the mother's daily diet and feeding type, focusing on CO_2_ emissions (climate change) and water consumption (as well as water scarcity), will be calculated based on ISO 14040 and 14,044, and other related ISOs [30–32]. To analyse the environmental data, a comparative life cycle study will be conducted considering the carbon footprint and, additionally, resource depletion (water consumption and scarcity) as environmental indicators, among others [30–32].

The environmental impacts (climate change, water consumption, and water scarcity) of the infant feeding types and maternal diet will be calculated using the IPCC [30], ReCiPE [31], and AWARE [32] validated methods, respectively.

The results of environmental impacts will be presented considering the following groups (Fig. 1):Feeding type and accessories used for infant feeding: EBF, FF, or MFThe mother's diet and food consumption habits.

**Fig. 1 Fig1:**
[figure not shown]
Environmental impact factors considered in the GREEN MOTHER I project. Legend: EBF – exclusive breastfeeding; MF – mixed feeding; FF – formula feeding

For the descriptive statistics, the qualitative variables will be described with their absolute and relative frequencies and quantitative variables with their mean and standard deviation or with their median and quartiles. In the comparison of proportions, we will use the Pearson Chi Square test and in the comparisons in quantitative variables the analysis of variance or the Kruscal-Wallis test (with post-hoc analyses), depending on the conditions of application. The level of significance will be 5% and the analyses will be performed with the statistical package STATA v.18.

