### Study design

This is a multicentre, cross-sectional study conducted in the Barcelona North Metropolitan Area (Catalonia, Spain) of the Catalan Health Institute (ICS), which provides universal coverage. The participating sites are the primary care settings of Sabadell, Granollers, Santa Coloma de Gramanet, Mollet, Mataró, Badalona, and Sant Adrià.

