### Recruitment

Midwives from the participating centres recruit women at one of their last pregnancy check-ups (or first postpartum visit) during November 2022 and May 2023. Those who meet the inclusion criteria and agree to participate in the study should be informed about the project and asked to sign the informed consent.

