### Procedure

In order to calculate the environmental impacts of the different types of infant feeding, the necessary variables are first to be collected in different questionnaires. Subsequently, the impacts of the types of breastfeeding will be calculated by adding together the impacts associated with the use of accessories, artificial milk and the mothers' diet for each type of infant feeding. The questionnaires are completed by the midwife during the visit with the mother.

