#### Data collection

Three questionnaires are to be prepared, using the REDCap platform [29]:Recruitment visit (indicating the moment in which they are recruited, visit week 38–40): Questionnaire concerning the socio-demographical data of mothers.Postpartum visit (7–10 days): Clinical data questionnaire – Newborn variables.Fortieth-day visit (4–6 weeks): Questionnaire on breastfeeding accessories and mother's nutrition variables.

All study variables are described in Annex II. Recruiting midwives are to be trained on how to complete the 24-h dietary recall and to be provided with a visual food atlas as support (Annex III) to help women record ration measurements.

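### The named tests treat women as independent although they are recruited and recorded by midwives in seven localities; the 5% level can be exceeded if feeding type and outcome both cluster

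*Protocol article*

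**What the plan says.** The tests are named in the statistical paragraph of the section Data analysis plan: "In the comparison of proportions, we will use the Pearson Chi Square test and in the comparisons in quantitative variables the analysis of variance". Kruskal-Wallis is the alternative for quantitative variables, post-hoc analyses follow, and the level is 5%. Neither that section nor Sample size calculation mentions site, centre, midwife, an ICC or a design effect.

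The same article describes a grouped design:

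- Study design: "The participating sites are the primary care settings of Sabadell, Granollers, Santa Coloma de Gramanet, Mollet, Mataró, Badalona, and Sant Adrià".
- Recruitment: "Midwives from the participating centres recruit women at one of their last pregnancy check-ups (or first postpartum visit").
- Procedure: "The questionnaires are completed by the midwife during the visit with the mother".
- Data collection: "Recruiting midwives are to be trained on how to complete the 24-h dietary recall", with a food atlas as support.

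Procedure also says that each feeding type's impact is the sum of the impacts of accessories, formula and the mother's diet. The recall recorded by the midwife is therefore part of the primary outcome.

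Prevalence of the three feeding types is the first secondary objective. For its presentation the plan says only that "the qualitative variables will be described with their absolute and relative frequencies". No confidence interval is mentioned.

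**The concern.** Pearson chi-square, one-way ANOVA and Kruskal-Wallis all take each woman as an independent observation. Women seen at the same centre or by the same midwife may be more alike than women chosen at random. They share an interviewer for the diet recall. They may also share local shops, food origin and transport, which the article collects, and a local population. If feeding type also differs between places, part of a difference between feeding groups is a difference between places, and the tests count it as if it came from independent women.

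Two things are at stake. The first is the 5% level of the comparisons of impact, diet and socio-demographic factors across feeding types. The second is the precision that a reader would attach to the prevalence figures, which are to form part of one of the two planned results papers.

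**Working it through.** **1. The plan's own figure.** Inputs from Sample size calculation: groups of 60, 60 and 30; difference 0.7; SD 1; alpha 5%; power 80%. One-way ANOVA power comes from the noncentral F distribution with 2 and 147 degrees of freedom and noncentrality λ = Σ nᵢ(μᵢ − μ̄)²/SD².

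- Means 0 / 0.35 / 0.7 (formula feeding at one extreme): λ = 10.29, power 81.9%.
- Middle group at the weighted mean of the other two, (60×0 + 30×0.7)/90 = 0.233: λ = (60×30/90)×0.7² = 9.8, power 79.9%.

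The stated size is reproduced for independent women with no allowance for clustering. The loss figure also agrees: 1 − 60/92 = 34.8%, against the stated 35%.

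**2. Level of the tests.** Feeding type varies between women within a site, so the usual design effect does not apply to these comparisons. The variance of a feeding-type contrast is inflated roughly by 1 + (m − 1) × ICC(feeding) × ICC(outcome), where m is the cluster size. With 400 women in 7 clusters, m ≈ 57:

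- both 0.02: 1 + 56 × 0.0004 = 1.02
- both 0.05: 1 + 56 × 0.0025 = 1.14
- feeding 0.05, outcome 0.10: 1 + 56 × 0.005 = 1.28
- feeding not clustered: 1 + 56 × 0 = 1, so no inflation

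Simulation used about 400 women, the article's expected split of 64/23/13%, no true association and 6,000 runs per setting (Monte Carlo standard error √(0.05×0.95/6000) ≈ 0.3 points). All ICCs are assumed. True error of a nominal 5% test:

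| Clusters | ICC feeding | ICC outcome | ANOVA | Chi-square |
|---|---|---|---|---|
| 7 | 0 | 0.02–0.10 | 4.5–5.4% | 4.8–5.2% |
| 7 | 0.02 | 0.02 | 5.4% | 5.3% |
| 7 | 0.05 | 0.05 | 6.7% | 7.4% |
| 7 | 0.05 | 0.10 | 8.8% | 9.0% |
| 7 | 0.10 | 0.10 | 12.5% | 13.5% |
| 40 of 10 women | 0–0.10 | 0–0.20 | 4.7–6.7% | 4.7–6.2% |

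In a further simulation of the same kind, a linear model with site as a fixed effect held about 5% throughout.

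**3. Prevalence.** Here one clustered variable is enough. Inputs: exclusive breastfeeding 64% and 408 women; seven sites give m = 408/7 ≈ 58.3. The simple half-width is 1.96 × √(0.64 × 0.36/408) = 4.7 points. The design effect is 1 + (m − 1) × ICC, and the half-width grows by its square root.

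| Assumed ICC | Design effect | Half-width (points) | Coverage of a simple 95% interval |
|---|---|---|---|
| 0.005 | 1.29 | ±5.3 | about 92% |
| 0.01 | 1.57 | ±5.8 | about 88% |
| 0.02 | 2.15 | ±6.8 | about 82% |
| 0.05 | 3.86 | ±9.2 | about 68% |

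**The case against.** The strongest reply has five parts.

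- **The tests are not shown to be too liberal.** A reader might infer that the 5% level fails outright. The documents do not support that. Both feeding type and outcome must cluster, and no ICC is given. At ICCs of 0.02, or with many small clusters, the error stays close to 5%. This stands and limits the conclusion to a conditional one.
- **No prevalence interval is planned.** One might read the plan as containing intervals that are too narrow. It contains none, only frequencies. This stands: the figures in step 3 describe what a simple interval would do if one were added.
- **The mechanisms are partly inferred.** It is tempting to say that midwives support breastfeeding in Phase I and so shape feeding type. The Background speaks of professional support only in general terms, and the support intervention belongs to Phase II. Nor does the article say that one midwife follows a woman through all three visits. Midwife training and the food atlas should reduce interviewer differences. All this stands; what remains documented is that midwives recruit the women and record the data.
- **Seven clusters may be close to the worst case.** The article names seven localities with primary care settings, and gives no count of centres or midwives. Clustering mainly at a lower level would mean smaller clusters and less inflation. This stands.
- **A journal article condenses the plan, and a fuller one may add site terms.** That is possible. But the article does name its tests, and the structure that they ignore is described in the same article.

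**Conclusion.** The point holds in conditional form. The stated tests and sample size take no account of the site and midwife structure that the article itself describes. Whether this matters depends on quantities that the article does not give. With seven clusters, the error of a nominal 5% test is about 5.4% if both ICCs are 0.02, and about 7–9% if feeding type has 0.05 and the outcome 0.05–0.10. With 40 clusters of 10 women there is little or no inflation. A simple interval on exclusive breastfeeding prevalence would understate its half-width by about 0.6 points at ICC 0.005 (5.3 − 4.7) and 4.5 points at ICC 0.05 (9.2 − 4.7).

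These figures assume equal cluster sizes, the expected 64/23/13% split and little loss of women. The prevalence figures also treat the seven localities as a sample of the places for which the result is meant to speak. The sample size calculation is not wrong on its own terms; it reproduces for independent women. The correction is worth making because it is cheap and changes little if the ICCs prove negligible.

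**What to change.** - **Impacts and diet across feeding types:** use a linear model with feeding type and site as fixed effects. Where Kruskal-Wallis would have been chosen, fit the same model on a transformed or rank scale.
- **Midwife:** add a midwife random intercept or midwife-clustered variance only if that identifier was recorded. The article does not document one, and Ethics and safety says that data are collected anonymously. Recruitment was set to run to May 2023, so the identifier may not be recoverable.
- **Feeding type against socio-demographic and clinical factors:** replace the plain Pearson test by a site-stratified or site-adjusted test.
- **Prevalence:** give cluster-adjusted 95% intervals for all three feeding types. If the seven sites are the clusters, use a small-sample correction, since only 7 − 1 = 6 degrees of freedom are then available.
- **Reporting:** state the number of centres and midwives, and report the observed ICCs.

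The cost is a few sentences of analysis text, a site variable in the data set, somewhat wider intervals, and six degrees of freedom for seven sites.

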### Sample size calculation

For the calculation we took into account both the local data on prevalence of three infant feeding types at month 1 [21] and the data provided by the literature for the footprint for consumption of 1 kg powdered breastmilk substitute for the nearest geographical area. This is 11 kg CO2 equivalents and standard deviation 1 in UK/France [1]. Accepting an alpha risk of 5% and a power of 80%, in a two-tailed test, a minimum of 60 subjects are necessary in the EBF group, 60 in the mixed and in 30 in the FF group to recognize as statistically significant a difference greater than or equal to 0.7 units (One-Way ANOVA menu, StudySize 2.0) [28]. The common standard deviation is assumed to be 1 [1] (One-Way ANOVA menu, StudySize 2.0, [28]).

These 150 women (60 + 60 + 30) are the minimum number we need to recruit. However, at the time of recruitment, we do not know which breastfeeding arm each of the participating women will be in during the follow-up month. From our own previous studies [21], we know that after one month of follow-up, from an initial recruitment of 400 women, some 256 (64%) could be breastfeeding exclusively, 92 (23%) using mixed and 52 (13%) a formula feeding [21]. These expected female counts exceed the required minimums in each arm, and would allow replacement rates for losses during follow-up of up to 35%.

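### Neither named test, ANOVA or Kruskal-Wallis, controls error for comparing means if spread differs across feeding groups, as is likely for the formula component; Welch's ANOVA would, at almost no cost

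*Protocol article*

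**What the plan says.** All references are to the protocol article.

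- **Tests.** The Data analysis plan names two tests for quantitative variables: "in the comparisons in quantitative variables the analysis of variance or the Kruscal-Wallis test (with post-hoc analyses), depending on the conditions of application". The significance level is 5%. The conditions, the post-hoc method and confidence intervals are not specified.
- **Variance assumption.** Sample size calculation states: "The common standard deviation is assumed to be 1". The value comes from "the footprint for consumption of 1 kg powdered breastmilk substitute for the nearest geographical area", not from a per-woman outcome.
- **Group sizes.** The same section expects that, of 400 women, "some 256 (64%) could be breastfeeding exclusively, 92 (23%) using mixed and 52 (13%) a formula feeding".
- **Outcome.** Under Procedure, each impact is the sum of accessories, formula and maternal diet. Under Independent variables, formula volume is recorded for MF and FF only.
- **Presentation.** Results are shown for "Feeding type and accessories used for infant feeding" by group, and separately for the mother's diet.

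**The concern.** A woman who breastfeeds exclusively contributes no formula, so that component has mean 0 and SD 0 in the EBF group. In MF and FF it varies with daily volume. Where feeding and accessories are shown apart from diet, day-to-day variation in diet cannot even out the spread.

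The groups are expected to be about 5:2:1 (256/52 = 4.9; 92/52 = 1.8). If the large group varies least, the pooled variance is pulled towards its small value and understates the uncertainty of the small groups. ANOVA then rejects too often. Kruskal-Wallis does not repair this: if spreads differ, it can reject although the means are equal. At stake are the p-values for the impact outcomes, and above all the precision claimed for contrasts that involve the small MF and FF groups.

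**Working it through.** **1. The plan's own figure.** The stated design is "Accepting an alpha risk of 5% and a power of 80%, in a two-tailed test", with "a minimum of 60 subjects are necessary in the EBF group, 60 in the mixed and in 30 in the FF group", a difference of 0.7 and SD 1. One-way ANOVA power comes from the noncentral F with λ = Σ nᵢ(μᵢ − μ̄)²/σ².

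- Means 0/0.35/0.7 (EBF/MF/FF): μ̄ = (60×0 + 60×0.35 + 30×0.7)/150 = 0.28. λ = 60×0.0784 + 60×0.0049 + 30×0.1764 = 10.29. Power is 81.9%.
- Means 0/0/0.7: μ̄ = 0.14. λ = 120×0.0196 + 30×0.3136 = 11.76. Power is 86.9%.

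The stated 80% is reproduced under equal SDs. The arithmetic is not in question; the common SD is.

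**2. From formula spread to SD ratio.** Let everything except formula have SD 1 in all groups, and let formula add an independent SD of ρ in MF and FF only. The SD ratio MF or FF to EBF is √(1 + ρ²): 1.02 for ρ = 0.2, 1.12 for ρ = 0.5, 1.41 for ρ = 1 and 2 for ρ = 1.73. The documents do not give ρ, so the ratios below are assumptions.

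**3. Type I error.** Normal data, equal means, groups of 256/92/52, 20,000 simulated studies per row. The check-then-test rule uses Levene's test (median-centred) and goes to Kruskal-Wallis if it rejects, otherwise to ANOVA.

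| SD EBF:MF:FF | ANOVA | Kruskal-Wallis | Check, then test | Welch |
|---|---|---|---|---|
| 1:1:1 | 4.9% | 4.9% | 4.9% | 4.9% |
| 1:1.12:1.12 | 6.9% | 5.9% | 6.5% | 5.1% |
| 1:1.41:1.41 | 10.8% | 7.8% | 7.9% | 5.0% |
| 1:1.5:2 | 15.9% | 9.8% | 9.8% | 4.9% |
| 0.5:1:1 | 16.4% | 10.8% | 10.8% | 4.8% |
| 0.2:1:1 | 25.0% | 17.3% | 17.3% | 5.1% |
| 2:1.5:1 (reverse order) | 1.4% | 2.3% | 2.3% | 5.1% |

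The simulation standard error is at most about 0.3 points. After the 35% loss that the protocol allows for (256×0.65 = 166, 92×0.65 = 60, 52×0.65 = 34), every figure is within 1 point of the table.

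**4. Hand check on MF versus FF.** The pooled variance is s² = (255σ²_EBF + 91σ²_MF + 51σ²_FF)/397. When MF and FF share SD σ, a pooled 95% interval for their difference covers with probability about P(|Z| < 1.966·s/σ).

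- 1:1.41:1.41: s² = (255 + 142×2)/397 = 1.358; s/σ = √(1.358/2) = 0.824; coverage about 89%.
- 0.5:1:1: s² = (255×0.25 + 142)/397 = 0.518; s/σ = 0.720; coverage about 84%.
- 0.2:1:1: s² = (255×0.04 + 142)/397 = 0.383; s/σ = 0.619; coverage about 78%.

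Simulation gives 89%, 84% and 77%. So a comparison that involves no EBF woman inherits its error term largely from the EBF group.

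**The case against.** **The choice is conditional.** Equal variance is a usual condition for ANOVA, so on an ordinary reading the plan leaves ANOVA when spreads differ. This stands, and it means that the ANOVA column is not the plan's error rate. The check-then-test column is closer, and it still reaches 8% to 17% once the SD ratio is 1.41 or more.

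**Kruskal-Wallis is a valid test of identical distributions.** True. Its excess rejections are errors only if the result is read as a difference in means. The study compares impacts in kg CO2eq, m3 and m3eq, so that reading is the natural one.

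**Unequal spread is not guaranteed.** A reader might infer that variances differ by construction in the primary outcome. The documents do not support this. Diet enters the total in all groups, comes from a single 24-hour recall, and may dominate the spread. If formula SD is at most half that of the rest, the ratio is at most 1.12 and ANOVA error is about 6% to 7%. Even without diet, EBF spread is not zero, because pumps, storage bags, pads and other accessories vary between breastfeeding women.

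**Equality of EBF and FF on formula is implausible.** This stands too: a false-positive rate matters little for that contrast. MF versus FF remains open.

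**The full analysis plan may name a post-hoc method.** It may, and its absence from the article is no fault. The article does, however, already fix the two overall tests.

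**Conclusion.** The point holds in a limited form: the plan names two tests, neither suited to comparing means under the unequal spread that its own outcome definition makes likely. The case is clearest for the separately presented feeding-plus-accessories result and weakest for the total that includes diet.

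The size depends on SD ratios that the documents do not give. Over the assumed range 1:1.12:1.12 to 0.2:1:1, error is about 7% to 25% for ANOVA and about 7% to 17% for a variance check followed by Kruskal-Wallis, against about 5% for Welch. The direction is also an assumption: with the larger spread in EBF, ANOVA would be conservative (about 1% at 2:1.5:1).

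Two stronger conclusions should not be drawn. A reader might infer that the study's intervals are wrong; the article plans none, so the coverage figures apply only if pooled-variance intervals are used. A reader might also infer that a rank test would leave the study unable to state the saving; group means in physical units can be reported whichever test supplies the p-value.

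This is a cheap improvement, not a demonstrated error.

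**What to change.** For the impact outcomes (climate change, water consumption, water scarcity), replace the choice between ANOVA and Kruskal-Wallis by Welch's ANOVA with Games-Howell pairwise contrasts. Linear regression on feeding type with HC3 robust standard errors is an equivalent route (in Stata, regress with vce(hc3)). Report mean differences in kg CO2eq, m3 and m3eq with 95% confidence intervals, by bootstrap if the data are strongly skewed. The analysis should not rely on the common SD assumed in the sample size calculation.

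The change takes one sentence and needs no new data. With equal variances, simulated power was 45.8% for Welch against 46.5% for ANOVA at a range of means of 0.3 SD, and 71.5% against 72.0% at 0.4 SD: under one percentage point lost.
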